#### Criteria for discontinuing or modifying allocated intervention/comparator

2.4.2

Discontinuation or modification of the allocated herbal medicine may occur under the following conditions:Development of clinically significant adverse events, including allergic reactions to herbal components or worsening gastrointestinal symptoms judged to be related to the study medication.Participant request to stop or change the assigned intervention at any time, without prejudice to subsequent medical care.Marked deterioration of functional dyspepsia symptoms requiring additional treatment outside the trial protocol.Investigator decision based on medical judgment, protocol non-compliance, or new contraindications (e.g., pregnancy).

Participants discontinuing the allocated intervention will, wherever possible, be encouraged to remain in the trial for outcome assessments to minimize attrition bias.

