##### Prohibited concomitant medications and treatments

2.4.3.2

The use of new medications or treatments specifically for dyspeptic symptoms is prohibited during the study. If such use occurs, the principal investigator will determine whether the participant should be withdrawn from the trial or excluded from the statistical analysis. The use of antibiotics is strictly prohibited during the study period. Probiotic preparations may be permitted if participants have been taking them continuously for at least 1 month before screening and if the dosage and regimen remain unchanged during the trial. Any change in dosage or regimen during the trial will be considered a protocol violation, and the participant will be withdrawn from the study.

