#### Safety evaluation variables

2.5.3

Liver function tests (AST, ALT) and renal function tests [blood urea nitrogen (BUN), creatinine (Cr)] will be conducted at screening and at week 8, requiring participants to fast for at least 8 h beforehand. Vital signs, including blood pressure (systolic and diastolic), pulse rate, and body temperature, will be measured. Blood pressure and pulse rate will be recorded in a seated position using an electronic sphygmomanometer after a minimum of 3 min of rest, except during telephone visits. Body temperature will be measured with an electronic thermometer after blood pressure measurement. Adverse events will be collected through participant self-reporting or investigator observation during the clinical trial.

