#### Exploratory evaluation variables

2.5.4

Korean medicine diagnostic devices, including an HRV analyzer, tongue diagnosis device, pulse analyzer, and abdominal examination device, will be used. HRV is a non-invasive tool for assessing health status by measuring sympathetic and parasympathetic activity. Kyung Hee University Hospital at Gangdong will use the SA-6000 (MEDICORE Co., Ltd., Republic of Korea), while Dongguk University Ilsan Oriental Medical Hospital will use the SA-3000NEW (MEDICORE Co., Ltd., Republic of Korea). The tongue diagnosis system (CTS-2000, Daeseong Medical Device, Republic of Korea) will evaluate tongue coating thickness, distribution, and color. The pulse analyzer (DMP-Lifeplus, Daeyo Medi Co., Ltd., Republic of Korea) will provide cardiovascular and pulse wave information. The abdominal examination device (Digital Algometer FPX25, Wagner Instruments, United States) will assess tenderness at nine abdominal acupoints: CV-14, CV-12, left/right ST-20, left/right ST-25, CV-4, and left/right ST-28. Stool and saliva samples will be collected at baseline (week 0) and post-treatment (week 8) for gut microbiome and fecal metabolite profiling and for oral microbiome analysis, respectively.

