#### Statistical analysis and evaluation of efficacy endpoints

2.8.2

The primary efficacy endpoint is the between-group difference in the GIS score at week 8 (ACCORD vs. DISCORD). The primary endpoint will be analyzed using the MMRM, with treatment group and visit time as fixed factors and participant as a random factor.

The secondary efficacy endpoints include TDS, AR for dyspepsia, OTE, dyspepsia VAS, FD-QoL, Spleen Qi Deficiency Questionnaire, Stomach Qi Deficiency Questionnaire, Food Retention Questionnaire, Cold–Heat Pattern Questionnaire, and Deficiency–Excess Pattern Questionnaire. Categorical secondary variables will be analyzed using the chi-square test or Fisher’s exact test.

To address the issue of multiple comparisons for the multiple secondary efficacy endpoints, the Benjamini-Hochberg procedure (False Discovery Rate, FDR) will be applied to adjust the *p*-values. The primary endpoint will be tested at a significance level of 0.05 without adjustment. Exploratory outcomes will not be adjusted for multiplicity, and their results will be interpreted as hypothesis-generating.

Exploratory subgroup analyses (by assigned herbal formula and by DISCORD subgroup) will be performed to assess the consistency of treatment effects; these analyses are hypothesis-generating and are not powered for confirmatory inference. Effect modification will be explored using treatment-by-subgroup interaction terms within the mixed model, and results will be reported as effect estimates with 95% confidence intervals and interpreted cautiously.

For the primary outcome, missing data will be handled using the last observation carried forward (LOCF) method. In addition, multiple imputation will be applied as a sensitivity analysis to assess the robustness of results under different assumptions regarding missingness. The main analyses will be conducted on an intention-to-treat basis, with per-protocol analyses performed for comparison.

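### Minor: withdrawing every participant who changes a probiotic discards obtainable week-8 GIS scores and safety bloods; rewording one sentence would keep them

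*Protocol article*

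**What the plan says.** Section 2.4.3.2 permits probiotics taken continuously for at least a month before screening, provided nothing changes during the trial. On a change, it says: "Any change in dosage or regimen during the trial will be considered a protocol violation, and the participant will be withdrawn from the study". The investigator has no discretion. In the same section, starting a new dyspepsia treatment leads only to a decision by the principal investigator.

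Section 2.4.2 lists grounds for stopping or modifying the allocated medicine, including an investigator decision for protocol non-compliance. It says that participants who stop will, where possible, be "encouraged to remain in the trial for outcome assessments to minimize attrition bias".

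Section 2.8.2 sets the analysis: "The main analyses will be conducted on an intention-to-treat basis, with per-protocol analyses performed for comparison". For the primary outcome, "missing data will be handled using the last observation carried forward (LOCF) method", and "multiple imputation will be applied as a sensitivity analysis to assess the robustness of results". Table 1 schedules GIS at screening, week 4 and week 8.

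Section 2.5.3 says that AST, ALT, BUN and creatinine "will be conducted at screening and at week 8", and section 2.8.3 compares them before and after treatment. Table 1 marks the blood test at screening only, but sections 2.1.1 and 2.5.3 both give week 8, and I follow them.

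A likely reason for the strict rule is in section 2.5.4, among the exploratory variables: "Stool and saliva samples will be collected at baseline (week 0) and post-treatment (week 8) for gut microbiome and fecal metabolite profiling", with oral microbiome analysis from the saliva.

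**The concern.** The rule makes the protocol, not the participant, the cause of missing data. Someone who stops the trial medicine is encouraged to attend at week 8; someone who takes every packet but alters a probiotic must leave. The second person remains in the intention-to-treat set, so a carried-forward GIS stands in for a score that could have been observed. Multiple imputation would test this, but only as a sensitivity analysis. The pre-post safety comparison may also lose the week-8 bloods.

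The likely purpose, clean microbiome and metabolite data, concerns exploratory outcomes. Excluding the participant from those analyses would serve it without giving up the primary endpoint.

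**Working it through.** **1. Does any other text keep these participants in follow-up?** No. The retention sentence in section 2.4.2 covers people who discontinue the allocated intervention. A site might try to treat a probiotic change as non-compliance under that section, but section 2.4.3.2 orders withdrawal from the study.

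**2. What is carried forward?** With GIS at screening, week 4 and week 8, withdrawal before week 4 leaves only the screening score. Withdrawal after week 4 and before week 8 leaves the week-4 score.

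**3. The plan's own sample size.** Section 2.7 gives 2.72, SD 4.57, 45 per group and 10% dropout; section 2.8 gives two-sided 5%. I assume 80% power, which section 2.7 does not state, and read 2.72 as the between-group difference.

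- n per group = 2 × (1.960 + 0.842)² × (4.57/2.72)² = 44.3, rounded up to 45.
- 45/0.9 = 50 per group, 100 in total. The stated figures are reproduced.
- Losses planned for: 100 − 2 × 45 = 10.

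**4. How many participants are affected?** The documents give neither the share using probiotics nor the share of users who change them, so both are assumed. Number = 100 × share using × share changing.

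| Using | Changing | Affected of 100 |
|---|---|---|
| 5% | 5% | 0.25 |
| 10% | 10% | 1 |
| 20% | 20% | 4 |

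**5. Shift in the result if a carried value is wrong.** Suppose it misses the true week-8 score by one SD (an assumption), with 50 per arm.

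- One value: 4.57/50 = 0.091 points; 0.091/2.72 = 3.4%.
- Four values, all in one arm and all in the same direction: 4 × 4.57/50 = 0.366 points; 0.366/2.72 = 13.4%.
- Four values, two per arm, same direction: the between-group shift is 0.

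**6. Power if the values were simply missing, over and above the 10 planned losses.** Normal approximation: SE = 4.57 × √(1/n₁ + 1/n₂), z = 2.72/SE, power = Φ(z − 1.96).

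| Evaluable | SE | z | Power |
|---|---|---|---|
| 45 vs 45 | 0.963 | 2.823 | 80.6% |
| 45 vs 44 | 0.969 | 2.807 | 80.2% |
| 43 vs 43 | 0.986 | 2.760 | 78.8% |

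If only the 90% who would otherwise complete can be lost this way, four withdrawals remove 3.6 values. That leaves (90 − 3.6)/2 = 43.2 per arm, and power is 79.0%.

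**The case against.** The strongest case is that this is a deliberate choice with negligible effect.

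- **No strict contradiction.** Section 2.4.2 speaks of people who stop the trial medicine, and section 2.2.2 admits probiotic users only if no dosage change is planned, so the rule enforces an entry condition. This stands: the two rules fit badly together but do not contradict each other.
- **The rule may protect the primary outcome too.** Bloating is one of the ten GIS items (section 2.5.1), and a probiotic change could affect it. This is a fair point. Under intention-to-treat, though, the observed score is normally preferred to a carried-forward one, and the planned per-protocol analysis addresses the contamination.
- **Withdrawal assessments may exist.** A full protocol often specifies them and an article often leaves them out. If GIS and bloods are taken at withdrawal, less is lost. The loss of safety bloods is therefore possible rather than established, but a true week-8 GIS would still be missing.
- **The size is assumed and partly double-counted.** If the 10% dropout allowance already covers these withdrawals, power does not fall below plan. LOCF also fills the values, so the power figures describe a different scenario from the main analysis. The 0.37-point shift needs the top of both assumed ranges, all four participants in one arm and every error in the same direction. All of this stands and keeps the point minor.
- **The larger issue is LOCF itself.** It applies to every dropout, and this rewording does not change it. That is true, but it is no reason to create extra missing values.

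**Conclusion.** The concern holds as a minor one. The rule removes a participant from the study for a reason that need not prevent assessment, and nothing else in the article keeps that participant in follow-up. It works against the plan's own retention aim and its intention-to-treat analysis.

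Under the assumed frequencies about one participant is affected (range 0.25 to 4). In the central case one arm mean could shift by about 0.09 points, or power could fall by about 0.4 percentage points (80.6% to 80.2%). In the extreme case the shift is 0.37 points or the power 78.8%. These figures rest on the assumed frequencies, the one-SD error, and reading 2.72 as the between-group difference. The direction of any bias cannot be determined from the documents.

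Only established users with no planned dosage change enter, multiple imputation gives a check, and adverse events are recorded at visits up to withdrawal. The trial's conclusion is not at risk.

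**What to change.** Replace the withdrawal sentence in section 2.4.3.2 with, for example:

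> If a participant alters the dose or schedule of a probiotic, this is recorded as a protocol deviation. The participant continues all scheduled assessments to week 8 and stays in the intention-to-treat analysis, but is left out of the per-protocol and the microbiome and metabolome analyses.

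Decisions about the study medicine stay with the clinical team under section 2.4.2.

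The cost is one sentence, with approval by both IRBs and a registry update if the change counts as substantial (section 2.11). No visits or procedures are added. The downside is that a few GIS scores collected after a probiotic change enter the primary analysis; the planned per-protocol analysis is the check. If this section is amended for any other reason, make the change then.

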#### Strategies to improve and monitor adherence

2.4.4

At the baseline visit, participants will receive detailed education on the prescribed dosage regimen and the importance of adherence to the study protocol. To enhance adherence, participants will receive reminder calls during the telephone visits (weeks 2 and 6).

Adherence will be monitored at visits 4 (week 4) and 6 (week 8). Participants are required to return all unused medication packets. Adherence will be calculated as the percentage of packets actually taken relative to the number of packets prescribed: (Total packets dispensed - Total packets returned) / (Total packets scheduled to be taken) × 100%. Participants with less than 70% adherence may be excluded from the per-protocol analysis, and reasons for non-adherence will be documented.

### Outcomes and data collection

2.5

All instruments used for primary and secondary efficacy endpoints have been previously validated with established reliability and validity in the target population, as detailed below.

#### Primary efficacy endpoint: GIS score

2.5.1

The GIS score assesses 10 gastrointestinal symptoms: nausea, retching, vomiting, bloating, abdominal cramping/discomfort, early satiety, acid reflux/heartburn, loss of appetite, retrosternal discomfort, and epigastric or upper abdominal pain. Each symptom will be rated on a 5-point Likert scale (0–4), and the total score will be calculated by summing the individual scores (20).

#### Secondary efficacy endpoints

2.5.2

##### Total dyspepsia symptoms

2.5.2.1

TDS consists of eight items related to dyspeptic symptoms, including postprandial fullness, bloating, early satiety, epigastric pain, epigastric burning, nausea, vomiting, belching, and other dyspepsia-related symptoms. Each item will be rated on a 4-point Likert scale (0 = none, 1 = mild, 2 = moderate, 3 = severe). The total score, obtained by summing the item scores, indicates the severity of dyspepsia, with higher scores reflecting more severe symptoms (16).

##### Adequate relief for dyspepsia

2.5.2.2

AR is a commonly used measure in FD evaluations. Participants will be asked whether their dyspepsia-related pain or discomfort has been adequately relieved since the last treatment, responding “yes” or “no.” Responders will be defined as participants answering “yes” to the AR question in at least 50% of assessments over the 8-week trial period. The responder rate will be compared between groups (21).

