**Methods:**

This study is a randomized, assessor-blinded, parallel-group, open-label, multicenter clinical trial. A total of 100 patients with FD will be recruited from two Korean medical hospitals and randomly assigned to either the ACCORD group (*n* = 50), which will receive treatment guided by the machine learning algorithm, or the DISCORD group (*n* = 50), which will receive one of the two treatments not recommended by the algorithm. Patients will take the assigned herbal medicine for 8 weeks, three times daily, between meals.

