The ground truth (target variable) for model training was the observed change in the Gastrointestinal Symptom (GIS) score from baseline to 8 weeks in the preliminary study. The models were trained using comprehensive baseline data as input features. These features included demographics (e.g., age, sex, and FD duration); patient-reported outcomes and questionnaires (e.g., GIS, and various pattern identification questionnaires); data from Korean medicine diagnostic devices (e.g., tongue diagnosis system, radial pulse analyzer, and digital algometer readings); and laboratory test results (e.g., blood chemistry).

During development, the dataset was split into training (80%) and test (20%) sets for internal validation. Hyperparameter tuning was conducted using RandomizedSearchCV with 5-fold cross-validation on the training data. To mitigate overfitting due to high data dimensionality, an iterative feature selection process was employed to enhance model robustness. The final models demonstrated robust predictive accuracy on the independent test set, confirming their capability to predict treatment responses and discriminate the relative effectiveness among the herbal formulations. Detailed methodology of the algorithm development is provided in Supplementary material 1. The algorithm for prediction system employed in this trial is a locked version (v1.1) that will not be updated during the study period. The prospective validation of this locked algorithm in a new cohort is essential for evaluating its generalizability and mitigating potential biases or overfitting inherent in the preliminary training dataset.

All groups will take the assigned clinical trial medications for 8 weeks. Participants will attend clinic visits at 4-week intervals until week 8 for evaluation of clinical variables, including vital signs, questionnaire surveys, and assessments with Korean medicine diagnostic devices (heart rate variability [HRV], tongue diagnosis, pulse diagnosis, and abdominal diagnosis). In addition, telephone visits will be conducted at 2-week intervals (weeks 2 and 6) to assess whether FD-related pain or discomfort has moderately improved since the previous treatment (Figure 1). Before and after taking the herbal medicine, blood samples (at screening and week 8) and stool and saliva samples (at weeks 0 and 8) will be collected to analyze blood and fecal metabolites as well as gut and oral microbiomes. A detailed assessment schedule is provided in Table 1.

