**Figure 1 fig1:**
[figure not shown]
Flowchart of the trial intervention. ML, machine learning; YJT, *Yijung-tang*; PWS, *Pyeongwi-san*; SST, *Shihosogan-tang*; GIS, gastrointestinal symptom.

**Table 1 tab1:** Clinical study schedule.

Assessment	Visit 1 (screening)	Visit 2 (baseline, week 0)	Visit 3 (week 2)	Visit 4 (week 4)	Visit 5 (week 6)	Visit 6 (week 8)
Written consent						
Demographic/medical history survey	●					
Physical measurements	●					
Vital sign measurements	●	●		●		●
Blood test	●					
Confirmation of inclusion / exclusion criteria	●					●
Random allocation		●				
Concomitant medications and adverse reaction confirmation		●	●	●	●	●
Gastrointestinal Symptom Score	●			●		●
Total Dyspepsia Symptom Score	●			●		●
Adequate relief of dyspepsia			●	●	●	●
Overall treatment effect				●		●
Dyspepsia Visual Analog Scale	●			●		●
Functional dyspepsia–related quality of life	●			●		●
Spleen Qi Deficiency Questionnaire	●			●		●
Stomach Qi Deficiency Questionnaire	●			●		●
Food Retention Questionnaire	●			●		●
Cold–Heat Pattern Questionnaire	●			●		●
Deficiency–Excess Pattern Questionnaire	●			●		●
Standard Tool for Pattern Identification of FD	●					
Korean medicine diagnosis (interview, tongue, pulse, abdominal)	●			●		●
Clinical trial medication prescription and administration education		●		●		
Clinical trial medication returns and compliance check				●		●
Stool kit and meal record sheet provision	●			●		
Stool sample collection, meal record sheet confirmation, and saliva sample collection		●				●
Confirmation of clinical study completion						●

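### The adequate-relief item has two thresholds, adequate relief in its definition and moderate improvement at the telephone visits, and its reference point is not a defined time

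*Protocol article*

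**What the plan says.** Four parts of the protocol article bear on this item.

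- **Endpoint definition (2.5.2.2, Adequate relief for dyspepsia).** Participants are asked "whether their dyspepsia-related pain or discomfort has been adequately relieved since the last treatment", with a yes or no answer. A responder is a participant "answering “yes” to the AR question in at least 50% of assessments over the 8-week trial period". Then: "The responder rate will be compared between groups".
- **Visit description (2.1.1, Study design and allocation).** After the four-weekly clinic visits, the text states that "telephone visits will be conducted at 2-week intervals (weeks 2 and 6") and gives their purpose as "to assess whether FD-related pain or discomfort has moderately improved since the previous treatment".
- **Schedule (Table 1).** One row, "Adequate relief of dyspepsia", is marked at weeks 2, 4, 6 and 8. The only other item marked at weeks 2 and 6 is the check of concomitant medications and adverse reactions.
- **Dosing (Abstract, Methods).** "Patients will take the assigned herbal medicine for 8 weeks, three times daily, between meals".

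Section 2.8.2 lists AR among ten secondary efficacy endpoints whose p-values are adjusted by the Benjamini-Hochberg procedure. Section 2.5 says the instruments for the primary and secondary endpoints have been validated.

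**The concern.** The two descriptions set different bars. Moderate improvement is a degree of change, whereas adequate relief is a judgement that the change is enough. A participant can be moderately better and still not adequately relieved. Nothing in the article reconciles the two.

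The responder rule gives all four answers equal weight, and half of them come from the telephone visits. If those visits use the looser wording, the responder rate mixes two questions according to how the participant was contacted, and it no longer measures what section 2.5.2.2 says it measures. AR is the only efficacy endpoint for which the article gives a responder definition.

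The reference point is a second, independent problem. Under continuous dosing, the last or previous treatment could mean the last packet, the last supply dispensed or the last contact. Participants who read it differently would be answering about different periods. The dyspepsia VAS (2.5.2.4), by contrast, has an explicit 2-week recall.

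**Working it through.** No sample size, power or alpha figure underlies this point, so there is no such figure to reproduce. The check has three parts.

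**1. Do the two sentences concern the same item?** Section 2.1.1 does not name AR. Table 1 marks two items at weeks 2 and 6: the medication and adverse reaction check, and AR. A telephone question about FD pain or discomfort can therefore only be the AR item. This link is inferred from the schedule and is not stated in the text.

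**2. What does the 50% rule allow?**

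- Scheduled AR assessments: weeks 2, 4, 6 and 8, so 4. By telephone: weeks 2 and 6, so 2.
- Threshold: at least 50% of 4, so at least 2 yes answers.
- Possible yes/no patterns: 2^4 = 16. Patterns with at least 2 yes: 6 + 4 + 1 = 11.
- One of the 11 is yes at weeks 2 and 6 with no at weeks 4 and 8: 2/4 = 50%, a responder.

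Two telephone yes answers are therefore sufficient, and one alone is not.

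**3. How far could the rate and the difference move?** The article gives no AR rates, so everything below is assumed: independent answers, a yes probability of c at each clinic visit and t at each telephone visit. Then

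P(responder) = 1 − (1−c)²(1−t)² − 2c(1−c)(1−t)² − 2t(1−t)(1−c)².

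The level within one arm:

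| c | t | P(responder) |
|---|---|---|
| 0.40 | 0.40 (one wording) | 1 − 0.1296 − 0.1728 − 0.1728 = 0.5248 |
| 0.40 | 0.50 | 0.6100 |
| 0.40 | 0.60 | 1 − 0.0576 − 0.0768 − 0.1728 = 0.6928 |
| 0.40 | 0.70 | 0.7732 |
| 0.30 | 0.30 (one wording) | 0.3483 |
| 0.30 | 0.40 | 0.4372 |
| 0.30 | 0.50 | 1 − 0.1225 − 0.1050 − 0.2450 = 0.5275 |
| 0.30 | 0.60 | 0.6192 |

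The gap between two arms:

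- **Clinic rates 40% vs 30%.** One wording: 52.48 − 34.83 = 17.65 points. Telephone rates 20 points higher in both arms: 69.28 − 52.75 = 16.53 points. The gap narrows slightly.
- **Clinic rates 20% vs 10%.** One wording: 18.08 − 5.23 = 12.85 points. Telephone rates 20 points higher in both arms (40% vs 30%): 34.72 − 17.47 = 17.25 points. The gap widens.

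So a looser telephone threshold raises the responder rate in each arm, but the sign of its effect on the difference depends on rates that the article does not give.

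**The case against.** The strongest defence is that section 2.1.1 is a narrative overview. It does not name AR, gives no question text and does not mention a yes/no answer. Table 1 has a single AR row across all four contacts, and the two sentences are built in parallel, which suggests a loose paraphrase of one instrument. The responder rule also counts answers to the AR question, which the same section defines as adequate relief. On that reading a reply about moderate improvement would not count, and the definition in 2.5.2.2 governs.

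This defence stands in part. It makes the responder consequence conditional on the 2.1.1 wording actually being used by telephone. It does not remove the contradiction in the published text, and it does not touch the undefined reference point, which is in the endpoint definition itself.

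Three stronger readings are tempting, and the document supports none of them.

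- A reader might infer that the mixed wording acts as random misclassification and pulls the arms together. A looser threshold at two fixed visits is a systematic shift, and the second two-arm example above shows the gap widening.
- A reader might take the reference point to be the packet swallowed a few hours earlier, so that steady relief is recorded as no. Nothing shows that participants would understand the item this way, and the case report form item and telephone script are not shown. What can be said is that the anchor is undefined.
- A reader might conclude that the result cannot be compared with adequate-relief results elsewhere. That rests on sources outside the document.

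**Conclusion.** The point holds as an inconsistency in how a secondary endpoint is described. One item has two thresholds, and its reference point is not a defined time under three-times-daily dosing.

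If the 2.1.1 wording is used on the calls, two telephone answers out of four meet the responder rule without any report of adequate relief. The document does not establish that this wording is in use. Under the assumed rates in the table, with telephone yes rates 10 to 30 points above the clinic rates, the responder rate within an arm would rise by about 9 to 27 points. That range is an illustration, not an estimate.

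The wording applies to both arms and does not by itself favour either, and its effect on the between-group difference has unknown direction. The primary GIS comparison and the sample size are unaffected. It should be corrected because question wording is fixed at data collection: an analysis plan cannot repair answers given to a different question.

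**What to change.** - Align section 2.1.1 with section 2.5.2.2, so that one identical yes/no adequate-relief question is asked at weeks 2, 4, 6 and 8, and check that the case report form item and the telephone script carry that wording.
- Replace the reference to the last treatment with one defined reference period consistent with the source instrument. Since the previous scheduled assessment is one option. A fixed number of days is another.
- If participants have already been asked a different wording by telephone, identify them and record which wording they received, so that the responder analysis can be examined with and without them.

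The cost is small: two sentences of protocol text, one form item and one script, with no added visit or assessment. If the question put to participants changes, section 2.11 may require approval by both review boards and an update of the two registries, since it treats changes to outcomes as an example of a substantial modification.
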